### Intervention

To identify eligible patients, a targeted review of patients’ medical record based on the inclusion and exclusive criteria will be carried out, with referrals from nurses or clinicians within the study site. During the formal screening session, we will ask patients to complete an initial screening assessment which includes age, educational background, diagnosis, heart function grade, etc. Patients who meet the study criteria will be asked to sign a written informed consent before attending the baseline visit. Participants’ baseline data includes patients’ general characteristics, health behaviors (daily diet, physical activities, smoking status) and medication adherence, as well as their blood pressure, blood glucose, blood lipid levels during hospitalization.

A total of 112 patients with coronary heart disease will be recruited at a clinical site and divided equally into an intervention group and a control group. All participants will be followed up for a total of one year (with three time-points for data collection).

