**Fig 1 pone.0300250.g001:**
[figure not shown]
The schedule of enrolment, interventions, and assessments *. *Recommended content can be displayed using various schematic formats. See SPIRIT 2013 Explanation and Elaboration for examples from protocols. **List specific timepoints in this row.

Patients will be included in the study if they: (a) are 18 years or older; (b) have a documented diagnosis of coronary heart disease including acute myocardial infarction (AMI) (Non ST and ST elevation MI), patients with unstable angina, and patients with stable angina; (c) have access to a computer, and (d) agree to participate.

The exclusion criteria include: patients who are (1) with a history of psychiatric and neurological disorders; (2) unable to speak or understand Arabic; (3) with impaired bilateral hearing, or visual impairment which limits the use of computers; (4) with contraindications or severe physical disabilities that limit patients from participation; Additional exclusion criteria will be applied if patients are not able to understand the procedure and the aims of the study after full explanation.

By using the results of a meta-analysis published in 2017 [5] for an incidence of a major cardiovascular event of 13.8% in the intervention group and 38.6% in the control group, with a power of 80% and a first-species risk α of 0.05, we found a size of 56 patients in each group.

All investigators in this study will attend rigorous training on data collection and research protocol.

Training sessions will be thorough, and detailed. The purpose of this rigorous training is to ensure that all investigators have a comprehensive understanding of the data collection methods and research protocols relevant to the study.

The research protocol encompasses the set of guidelines, procedures, and ethical standards that govern how the research study will be conducted. It includes considerations such as participant recruitment, informed consent, data handling, confidentiality, and data analysis methods.

These sessions will be held before the start of the survey to prevent measurement bias. In addition, all investigators are trained in the principles of therapeutic education.

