#### Secondary outcomes

The secondary outcomes of the study include changes in health behaviors (smoking cessation, adoption of a healthy diet, physical activity), medication adherence, cardiovascular health score and health-related quality of life which will be assessed using the validated Tunisian version of the SF-12 health survey [16].

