### Variable definitions

The American Heart Association defines the ideal cardiovascular health as simultaneous presence of four ideal health behaviors and three ideal metabolic indicators [17]. The four ideal health behaviors include nonsmoking, body mass index (BMI) < 25 kg/m2, physical activity at targeted level, and dietary consumption being consistent with current recommended guidelines. The three ideal metabolic indicators are identified as clinical parameters for blood pressure < 120/80 mm Hg, total cholesterol < 5.17 mmol/L (200 mg/dL) and fasting glucose < 5.60 mmol/L (100 mg/dL). Each component of the cardiovascular health metrics will be dichotomized as 1 (ideal status) or 0 (intermediate or poor status).

The validated Tunisian version of the SF-12 health survey (16) produces two summary scores: the Physical Component Summary (PCS) and the Mental Component Summary (MCS). These scores are standardized to have a mean of 50 in the general population, with a standard deviation of 10. Higher scores indicate better health-related quality of life.

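### Change in coronary-medication adherence is undefined for patients first diagnosed at the index admission, and three of seven cardiovascular health components start from in-hospital values; follow-up levels should be compared between arms instead

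*Protocol article*

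**What the plan says.** All references are to the protocol article.

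- **Baseline (Intervention).** Besides general characteristics, the data taken at baseline are "health behaviors (daily diet, physical activities, smoking status) and medication adherence, as well as their blood pressure, blood glucose, blood lipid levels during hospitalization". Patients "sign a written informed consent before attending the baseline visit"; that visit is not dated relative to discharge.
- **Eligibility (Settings and participants).** The diagnosis that qualifies a patient is "coronary heart disease including acute myocardial infarction (AMI) (Non ST and ST elevation MI), patients with unstable angina, and patients with stable angina". Neither earlier coronary disease nor earlier cardiac treatment is required.
- **Outcomes (Secondary outcomes).** "The secondary outcomes of the study include changes in health behaviors", and the same sentence goes on to medication adherence, the cardiovascular health score and quality of life. The Methods part of the Abstract has a similar list.
- **Score (Variable definitions).** Four behaviours (smoking, body mass index, activity, diet) and three metabolic indicators (blood pressure, total cholesterol, glucose) are each coded 1 or 0. The glucose criterion is "fasting glucose < 5.60 mmol/L (100 mg/dL").
- **Intervention-arm tests (Intervention group).** Lipids and glucose are requested at the last education session in order to judge the programme's medium-term effect. A further biological check-up follows 3 months after the programme ends. Both are described for the intervention arm only.
- **Analysis (Data analyses).** Two-group tests of means and percentages are named. No paired or baseline-adjusted method is named.

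**The concern.** A change outcome needs a baseline that means the same thing for every patient. For someone whose coronary disease is diagnosed at this admission, there was no coronary prescription to follow beforehand. Adherence to coronary drugs before the stay is therefore undefined, not high or low. The article collects baseline adherence from everyone and makes no distinction.

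The metabolic values have a milder form of the same problem. For acutely admitted patients they are taken during the event and compared later with values obtained after recovery and under treatment started at the admission. Each is cut at a fixed threshold, so a temporary shift can flip a component between 0 and 1.

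Two things are at stake:

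- The between-arm comparison of change may have to leave out patients with no baseline, or carry a baseline weakly related to follow-up.
- Any before-after change within the intervention arm would credit the programme with recovery and with new drug treatment. The article describes such a use: for the lipid and glucose tests meant to show the programme's effect, the only earlier values described are the in-hospital ones.

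**Working it through.** **1. The plan's own figure.** The only calculated figure is the sample size. Inputs: 13.8% and 38.6%, power 80%, alpha 0.05, here two-sided.

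- Pooled proportion: (0.138 + 0.386)/2 = 0.262. Difference: 0.248.
- Uncorrected: n = [1.960·√(2·0.262·0.738) + 0.842·√(0.138·0.862 + 0.386·0.614)]² / 0.248² ≈ 48.2, so 49.
- With continuity correction: n' = (n/4)·[1 + √(1 + 4/(n·0.248))]² with n = 48.2, giving about 55.9, so 56 per group.

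The stated 56 is reproduced. Nothing in it depends on when the secondary-outcome baseline is taken.

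**2. Share of the score affected.** In-hospital timing is stated for the three metabolic indicators only: 3/7 = 43% of the components. The other four are not stated to be in-hospital values.

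**3. Patients without a baseline for coronary-drug adherence.** The share p of first presentations is not given. Assume p from 0.40 to 0.70.

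- 112 × 0.40 = 44.8, about 45 patients.
- 112 × 0.70 = 78.4, about 78 patients.

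**4. Precision of a change score.** Let ρ be the correlation between baseline and follow-up, with equal variances. Relative to comparing follow-up values in the same patients:

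- variance ratio for a change score: 2(1 − ρ);
- variance ratio for a baseline-adjusted comparison: 1 − ρ².

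| ρ | Change score | Baseline-adjusted |
|---|---|---|
| 0 | 2.0 | 1.00 |
| 0.3 | 1.4 | 0.91 |
| 0.5 | 1.0 | 0.75 |
| 0.7 | 0.6 | 0.51 |

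Adjustment is never worse than ignoring the baseline. A change score is worse when ρ is below 0.5.

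**5. Both effects together, for adherence.** If change is analysed only in patients with a baseline, and the comparator is follow-up level in all patients, the standard error ratio is √[2(1 − ρ)/(1 − p)].

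| ρ | p = 0.40 | p = 0.70 |
|---|---|---|
| 0 | √(2.0/0.6) = 1.83 | √(2.0/0.3) = 2.58 |
| 0.3 | √(1.4/0.6) = 1.53 | √(1.4/0.3) = 2.16 |
| 0.5 | √(1.0/0.6) = 1.29 | √(1.0/0.3) = 1.83 |
| 0.7 | √(0.6/0.6) = 1.00 | √(0.6/0.3) = 1.41 |

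The range 1.3 to 1.8 is the ρ = 0.5 row. With a strong correlation and the lower share there is no loss; with a weak correlation the loss is larger.

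**6. Bias.** Whether a patient was treated before admission is fixed before allocation. Leaving untreated patients out therefore does not bias the contrast between randomised arms; it narrows the result to previously treated patients. In-hospital metabolic values are likewise common to both arms. Within one arm there is no such protection.

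**The case against.** The case on the other side has several parts.

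- **Adherence measured in hospital.** A reader might infer that baseline adherence is recorded while staff give the drugs, so that it is near 100% and can only fall. The text does not support this. The in-hospital phrase attaches most naturally to blood pressure, glucose and lipids, and the baseline visit is undated. The point rests only on adherence before the stay being undefined for newly diagnosed patients.
- **Whether adherence is a change outcome.** The word for change clearly governs health behaviours, and extending it along the list is a reading, though the most natural one. The planned two-group tests would fit a comparison of levels just as well. This stands as an ambiguity; it does not remove the need to fix the definition.
- **An acute-illness baseline for the whole score.** This is too broad. Three of seven components are affected, stable-angina patients need not be acutely ill, and the article gives no size or direction for any shift.
- **Fasting glucose.** A reader might see a contradiction between the baseline list and the score definition. The list may simply be shorthand, since it does not say the sample is non-fasting. A clarification is enough.
- **Other drugs.** First presenters may already take medication for other conditions, so the gap concerns coronary medication only.
- **Detail left elsewhere.** Recall period and instrument belong in the full protocol, and the schedule figure is not shown. That is fair and is not held against the article. What remains is a stated baseline, a stated population and a stated outcome that do not fit together for newly diagnosed patients.
- **Randomisation removes the harm.** It does for bias between arms, but not for within-arm claims. Data analyses plans no paired test, yet the Intervention group section does describe one-arm tests meant to show programme impact.

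**Conclusion.** The concern holds in a limited form. Change in coronary-medication adherence has no meaningful starting value for patients first diagnosed at the index stay, and 3 of 7 cardiovascular health components start from in-hospital values. It would go too far to conclude that the secondary comparisons between arms are biased. They stay valid under randomisation, provided follow-up is taken at comparable times in both arms.

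The cost to the between-arm comparison is possible loss of patients and precision. It cannot be fixed from the article because it depends on the unstated share of first presentations and on the correlation. Under the assumed 40% to 70%, the standard error ratio is 1.29 to 1.83 at a correlation of 0.5, and 1.00 to 2.58 over correlations from 0.7 down to 0. These figures assume equal variances and that every first presenter lacks a usable baseline.

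The firmer consequence concerns interpretation: a within-arm change from in-hospital values cannot be read as programme effect. The primary outcome and the 56 per group are untouched.

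**What to change.** 1. Define the adherence outcome as the between-arm difference in adherence level at 12 months, in all patients, and at any earlier time point measured in both arms. The 3-month assessment is described in the text for the intervention arm only, so it qualifies only if controls are also assessed then.
2. Record pre-admission adherence only as a descriptor for patients already on coronary treatment.
3. Compare the cardiovascular health score and its metabolic components between arms at follow-up, adjusted for baseline, rather than as change.
4. State that the baseline glucose is the fasting value that the score requires.
5. State that within-arm change from in-hospital values, including the intervention-arm lipid and glucose tests, will not be reported as evidence of programme effect.

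The cost is mostly wording, plus a regression adjustment and, if baseline glucose is not already fasting, the timing of a blood test already taken. The small downside is that adherence is no longer reported as a change. Sample size and primary analysis stay as they are.

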### Intervention group

Patients assigned to the intervention group will first receive therapeutic education. The digital platform will then enable care providers to support them remotely.

A questionnaire will be distributed to patients before they begin the TPE program, in order to assess their knowledge of the disease, their eating habits, their physical activity, etc.

The same questionnaire will be distributed again at the end of the intervention, to study the impact of the TPE program in terms of knowledge retention.

Participants assigned to the intervention group will be divided into sub-groups. Each group will receive three TPE sessions. Educational sessions will be held once every week.

TPE sessions will include theoretical presentations on the pathophysiology of coronary artery disease, its risk factors, therapeutic objectives and therapeutic management.

These sessions will also include practical workshops using video sequences, role-playing and card games, covering heart attack alert, biological and blood pressure therapeutic objectives, the Mediterranean diet, the different commercial presentations of drugs, and types of social coverage.

At the end of each session, a round-table discussion will be held on the daily life of a coronary sufferer: physical activity/stress management/smoking/returning to work.

During the last session, each patient will benefit from an individual interview during which a lipid and glycemic assessment will be requested to evaluate the impact of the TPE in the medium term.

In addition, each patient will receive leaflets in Arabic, summarizing what will be presented during the TPE sessions.

At 3 months after completion of the TPE program, the same questionnaire will be redistributed, a biological check-up will be requested, and a quality-of-life assessment will be carried out.

In a second phase, the intervention group will be monitored via a digital platform.

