**Methods:**

This study is a randomized controlled trial. Patients with coronary heart disease will be recruited from one clinical site and randomly assigned into two groups: the intervention group and the control group. All participants will be followed up for a total of one year (with three-time points for data collection). Patients who are assigned to the intervention group will receive therapeutic education at first. The digital platform will then allow healthcare providers to accompany them outside the hospital walls. The primary outcome is the incidence of major cardiovascular events within one year of discharge. Main secondary outcomes include changes in health behaviors, medication adherence, and quality of life score. The digital platform is a multi-professional telemonitoring platform that allows care teams to accompany the patient outside the hospital walls. It allows the collection and transmits information from the patient’s home to the therapeutic education team. All data will be secured at a certified host. The patient application provides data on compliance, adherence to physical activity (number of steps taken per day), adequate diet (weight gain, food consumed during the meal, compliance with low-salt or salt-free diet, diabetic diet), smoking cessation, as well as medication adherence. Access to educational tools (digital media) is provided to all initial program participants. These tools will be updated annually by the rehabilitation team on the recommendations. The platform also offers the possibility of organizing an individual or group remote educational session (videoconference modules allowing group and individual sessions), a secure integrated caregiver-patient messaging system. The control group will receive the usual controls at the hospital.

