At the end of the TPE program, the medical team verifies eligibility for the digital platform program. A "therapeutic support" contract is signed by the program participant and the medical team, setting out the therapeutic objectives during follow-up, as well as the parameters to be collected and transmitted to the platform.

The TPE team will educate the patient in the use of the mobile application, which is based on the codes and uses of consumer applications.

*Second step: digital monitoring phase*

Every day, the patient will be invited to transmit the monitoring parameters set out in the "therapeutic support" contract.

Data will be transmitted asynchronously and securely on the monitoring platform.

*Third step: Data analysis phase*

The medical team can interact with the patient via the platform. If necessary, the patient can be called into the center by the medical team for reassessment and early consultation, in order to optimize his or her care pathway.

*Forth step: Assessment phase*

At 12 months, an assessment of knowledge retention will be carried out, as well as the incidence of major cardiovascular events.

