### Control group

The control group will receive the usual controls at the hospital. Patients of the control group will not receive the TPE program neither a digital monitoring.

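### The 3-month secondary assessments are timed from completion of the education program, which controls never receive, so the arms may be compared at different times since hospitalisation

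*Protocol article*

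**What the plan says.** The Abstract states "Main secondary outcomes include changes in health behaviors, medication adherence, and quality of life score". The Secondary outcomes section adds a cardiovascular health score and names SF-12 as the quality-of-life instrument. Settings and participants, and again Intervention, promise every participant one year of follow-up with three data-collection time-points. The readable text does not say when these are.

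The dated 3-month follow-up stands under Intervention group: "At 3 months after completion of the TPE program, the same questionnaire will be redistributed, a biological check-up will be requested", with quality of life assessed at the same time. That section also sets three TPE sessions, one per week. The Control group section says "The control group will receive the usual controls at the hospital" and excludes controls from both TPE and digital monitoring.

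For participants in general, the baseline data include "health behaviors (daily diet, physical activities, smoking status) and medication adherence, as well as their blood pressure, blood glucose, blood lipid levels during hospitalization". SF-12 is not named there. The last platform step reads "At 12 months, an assessment of knowledge retention will be carried out, as well as the incidence of major cardiovascular events" and names no other secondary measure.

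The Primary outcome section gives each arm its own starting date: discharge for controls, TPE completion for the intervention group. Fig 1 is captioned as the schedule of assessments but is not shown in the text available here.

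**The concern.** A between-arm comparison of change needs the same interval in both arms. Here the only dated 3-month assessment is tied to an event that one arm does not have. The Primary outcome section shows that arm-specific clocks are a stated choice of the plan, so the wording under Intervention group cannot be put down to a slip.

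Eligible patients include those with acute myocardial infarction and unstable angina. If quality of life, activity or other behaviours shift during recovery, which is a reasonable assumption that the article does not quantify, a later visit in one arm adds elapsed time to the treatment contrast. Where the natural course is improvement, the extra time would favour the intervention arm.

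A second, smaller point concerns SF-12. Change in quality of life is promised, yet the readable baseline list does not name the instrument that would supply the starting value.

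**Working it through.** **The plan's own figure.** Settings and participants assumes event rates of 13.8% (intervention) and 38.6% (control) and reports its result thus: "with a power of 80% and a first-species risk α of 0.05, we found a size of 56 patients in each group". Sidedness is not stated; two-sided is assumed. With mean proportion (0.386 + 0.138)/2 = 0.262 and difference 0.248:

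- Uncorrected: n = [1.96 × √(2 × 0.262 × 0.738) + 0.842 × √(0.138 × 0.862 + 0.386 × 0.614)]² / 0.248² = 48.2, rounded up to 49.
- Continuity-corrected: (48.2/4) × [1 + √(1 + 4/(48.2 × 0.248))]² = 55.9, rounded up to 56.

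The stated 56 per group is reproduced. The present point does not touch it.

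**Timing gap.** Inputs: three sessions at weekly intervals (Intervention group); discharge as the control origin (Primary outcome), carried over to the secondary outcomes as an assumption; a wait of w weeks from discharge to the first session, not stated, taken as 0 or more.

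- First to last session: (3 − 1) × 1 week = 2 weeks.
- Intervention visit: discharge + w + 2 weeks + 3 months.
- Control visit: discharge + 3 months.
- Difference: w + 2 weeks.

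| Assumed wait w | Gap between arms |
|---|---|
| 0 weeks | 2 weeks |
| 2 weeks | 4 weeks |
| 4 weeks | 6 weeks |

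The effect of this gap on SF-12 or behaviour scores cannot be computed, because the article gives no rate of change over recovery.

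**Does a missing SF-12 baseline cost power under this plan?** Inputs: 56 per arm, SD 10 (the general-population norm in Variable definitions), two-sided 0.05, 80% power. The baseline-to-follow-up correlation r is an assumption.

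- Follow-up scores only: (1.96 + 0.842) × 10 × √(2/56) = 5.3 points.
- t-test on change: 5.3 × √(2(1 − r)) = 6.3, 5.3 and 4.1 points for r = 0.3, 0.5 and 0.7.
- Baseline-adjusted model: 5.3 × √(1 − r²) = 5.1, 4.6 and 3.8 points for the same r.

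Data analyses names Student's t-test or the Mann-Whitney test and no baseline-adjusted model. Under the named t-test, having a baseline makes the detectable difference larger, equal or smaller depending on r. The case for a baseline SF-12 is therefore that the stated outcome is a change, not that a known amount of power is lost.

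**The case against.** The strongest reply is that the assessment schedule is in Fig 1, which cannot be seen here. That figure may list control visits and a baseline SF-12, and a journal article commonly leaves visit detail to a figure or the full protocol. The readable text also promises three time-points to everyone, and the Primary outcome section collects events by a 12-month interview that is not limited to one arm. The Control group section describes care and need not list assessments. The baseline list is introduced as what the data include, so it is not closed.

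Most of this stands, and it rules out several stronger readings that a reader might infer:

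- That controls have no study assessments. The promise of three time-points to all participants contradicts this.
- That change cannot be computed for the secondary outcomes in general. Behaviours, adherence, blood pressure, glucose and lipids are listed at baseline for participants generally.
- That the quality-of-life effect cannot be estimated. Follow-up SF-12 scores could still be compared between randomised arms without a baseline.
- That a missing baseline raises the detectable difference from 4.6 to 5.3 points. That contrast presumes a baseline-adjusted analysis that the article does not plan.
- That the uncontrolled before-and-after knowledge questionnaire damages an endpoint. Knowledge is not among the listed secondary outcomes.

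The reply does not remove the timing rule. It is written in the text, and a schedule in Fig 1 could at most conflict with it.

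**Conclusion.** The point holds as one of unequal timing. The text ties the 3-month questionnaire, biological check-up and quality-of-life assessment to TPE completion, a date that controls lack. If controls are assessed from discharge, as the primary outcome is, the arms differ by 2 weeks plus the unstated wait for TPE. This rests on two assumptions: that the control clock for secondary outcomes follows the one for the primary outcome, and that the first session is not before discharge. The size of any resulting bias is unknown.

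On SF-12, the finding is only that the readable baseline list does not name it while change is promised; its absence from the trial is not shown. What the arm-specific origins do to the primary outcome itself is a separate matter and is not assessed here.

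**What to change.** Name the three data-collection points in the text and time them from one origin in both arms, such as randomisation. At those points, use the same questionnaire, laboratory tests and SF-12 in both arms. Write SF-12 into the baseline visit for both arms. If Fig 1 already shows these items, align the text with the figure.

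The cost is a 12-item form, and possibly control-arm laboratory tests if usual care does not already include them, at visits already promised to all participants. The baseline item is the urgent part, since a starting value not collected at the baseline visit cannot be recovered later.
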